### Hypotheses and statistical analysis

The two trials are separate and will be analyzed as such. We have three primary hypotheses for each trial: that the clinical question recorder will be more effective than the control; that the evidence retrieval coach will be more effective than the control; and that audit, feedback and gamification will be more effective than the control. Each of these hypotheses will be tested separately (half of the sample compared to the other half). The effect of each intervention will be tested by regressing the average number of searches per month over the trial’s six-month time period for each user onto dummy variables for each intervention, controlling for search frequency at baseline. The distribution of the number of searches per user is not known at present, but baseline data suggests excess zeros with extra-Poisson variation. We will attempt to capture the distribution parametrically, but in the event that it is not possible to do this accurately, we will use ordinary least squares to estimate the regression coefficients together with heteroscedasticity-robust standard errors.

### Potential subgroup effects

Prior to the start of the trial, we hypothesized that the impact of the intervention on our primary outcome may differ according to specialty type - *e.g*., more effective in clinicians practicing internal medicine than family medicine or other specialties - and according to baseline frequency of search during the six months prior to the trial - *e.g*., higher frequency searchers would tend to be more responsive to each intervention (see Table 5 for the baseline data for these two pre-specified subgroups). In an exploratory analysis, we will test for subgroup effects, using tests of interactions between the dummy variables for intervention and subgroup variables.

### Potential interactions between the interventions

Our primary analysis will be at the margins, that is, looking at each effect independently, but we will also test for interactions among the interventions. We expect that combining them will have an additive effect, and that an interaction is unlikely, particularly a sub-additive one (*e.g*., one intervention being effective alone, but less effective or even ineffective in combination with another). We cannot formally exclude any synergistic interaction (beyond additivity), but we have no reason to expect it *a priori*[46]. Moreover, observing a synergistic effect would not jeopardize our results, as we are more interested in finding any `signal’ of effect of the interventions, rather than estimating their independent effect with maximal accuracy. By analogy with drug trials, this study would be a phase II rather than a phase III randomized trial, given the current state of research in the field.

### Power calculation

Since we anticipated that interactions among the interventions are unlikely, we have powered the trials assuming no such interactions. Before the trials began, we had 904 participants eligible for the study, of whom 429 were postgraduates and 475 were faculty (see Table 5). Baseline data indicated a mean of 0.46 searches per month per user (SD 1.42) among postgraduates and 0.20 searches per month per used (SD 0.83) among faculty. Additional file 4 shows power curves for the faculty and for the postgraduates. These indicate that among the postgraduates, we will have 80% power to detect an increase of 0.9 in the mean number of searches per month, and among the faculty we will have 80% power to detect an increase of 0.5 in the mean number of searches per month.

### Analysis of secondary questions

An exploratory analysis will investigate time trends in intervention efficacy. Rather than using the average number of searches per user per month over the six months of the trial, we will conduct a longitudinal analysis using the number of searches per user for each of the six months of the trial as the dependent variable, regressed onto time, dummy variables for each of the interventions, the interaction between time and intervention, together with search frequency at baseline. This regression model will be fitted using a Generalized Estimating Equation (GEE).

Finally, we will compare the distribution of answers on the IAM questionnaire *(i.e*., utility, use and usefulness of the evidence retrieved), as well as the distribution of access to the different EBM resources, using chi-squared tests.

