### Outcomes

#### Primary outcome

Our primary question is whether each intervention increases the quantity of searches to answer questions - *i.e*., search utilization (not counting logins to e-mail alerts or to access other resources). This will be measured by (i) rate of searches/month/user, (ii) and corresponding proportions of `super-searchers’ (>five searches/month), `regular-searchers’ (one to five searches/month), `occasional-searchers’ (<one search/month), and `alert-only-users’ (no searches/month). The primary outcome will be averaged over six months, but continuously recorded as participants will be signed on through their individual user account that tracks logins and use of EBM resources, down to individual keystrokes.

Table 5 shows the baseline utilization data during the six months prior to the start of the trial, from July to December 2013. Postgraduates MDs (n = 429) searched MacPLUS FS 935 times in total, corresponding to about 0.46 searches/month/user, whereas they accessed 4,064 alerts to new evidence, corresponding to 1.65 alerts/month/user, and consulted other web-resources in MacPLUS FS 0.52 times/month/user. About 66.9% of postgrads users were `alert-only-users,’ while 10.5% were `regular-searchers’ and 1.9% `super-searchers.’

The utilization patterns were different for Faculty MDs (n = 475) who searched MacPLUS FS half as much, about 423 times in total, corresponding to about 0.20 searches/month/user, whereas they accessed almost twice as many alerts to new evidence, 7,092 alerts in total, corresponding to 2.54 alerts/month/user, and consulted other web-resources in MacPLUS FS 0.32 times/month/user. About 78.9% of faculty used were `alert-only-users,’ while 5.1% were `regular-searchers’ and 0.8% `super-searchers.’

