### Secondary outcomes and questions

We will assess whether each intervention can increase the utility of the evidence retrieved (satisfaction in meeting users’ information needs, expected impact on one’s general practice), the use of the evidence (the extent of use when caring for a specific patient), and its perceived usefulness in patient care and outcomes (perceived benefits of applying the evidence for a specific patient). Utility, use and usefulness of the evidence retrieved will be assessed using an adapted version of the Impact Assessment Method (IAM) [41]-[43], which was specifically developed for assessing how clinicians use information, based on the Acquisition-Cognition-Application-Outcome Model [42]-[44]. This validated six-item questionnaire takes less than one minute to complete online and will be sent by e-mail for online completion following a pre-defined automatic algorithm. The first invitation will be sent out one month after the participant’s first online exposure to one or more interventions, with one reminder after 24 hours. The next invitation will be sent following the next search, but after a two-week delay. This process will be repeated until one filled questionnaire for a clinical question is returned, or the trial ends (see details and full questionnaire in Additional file 3). Perceived usefulness will be analyzed as the `number needed to benefit from evidence,’ defined as the number of patients for whom the evidence has to be retrieved to observe or expect health benefits for one patient [45]*.*

Other secondary questions that we plan to address include whether each intervention efficacy varies across time within the six-month trial (*e.g*., persistent, transient, increasing or decreasing effect), and whether the interventions have an impact on non-searching utilization of MacPLUS FS (*i.e*., frequency of alerts read, frequency of web logins for other clinical resources).

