## Discussion

The three interventions in these two factorial randomized trials are innovative in at least three different ways. First, although widely used in other fields such as education, task management, business, or customer user-centered services, we are not aware that any of these approaches have been applied thus far to clinical evidence retrieval. Second, the interventions use web-based technology to facilitate low cost implementation at a broad scale, for all types of devices. Smartphones and tablets are transforming the way we live, practice medicine, and intuitively learn new skills [47],[48]. Third, the general framework for these interventions is based on effective models for teaching clinical skills at the point of care. These models have changed the way we teach clinical examination or diagnostic reasoning - embedded in our daily practice [30]-[34] - but have not yet been used to teach how to find current best evidence in the point of care, a skill that has nevertheless become designated `as essential as the stethoscope’ [8].

Our trials have also inherent limitations. First, although MacPLUS FS includes most top EBM resources currently widely used by clinicians (see Table 1), participants may still opt to access individual resources directly rather than through MacPLUS FS. However, although this may result in an apparent low frequency of search, the randomization should balance the distributions of such behaviors across study arms and not jeopardize the conclusion from the trials.

Second, although the validated IAM will try to capture the secondary outcomes of utility, use and perceived usefulness of the retrieved, these surveys may suffer from suboptimal response rates. Ideally, we would assess the effect on directly measured patient important outcomes, but this is beyond the feasibility of the current study, and particularly challenging at hospital-levels across a very wide array of potential clinical questions. In any event, the justification for doing a larger multi-centered trial with direct measurement of patient outcomes would be the observation of a sufficient utilization rate associated with a substantial effect on evidence use and usefulness in the present trial. By analogy with drug trials, this study would be a phase II trial.

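### The chi-squared comparison of returned IAM answers is not protected by randomisation, so it cannot show that an intervention increases utility, use or usefulness

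*Protocol article*

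**What the plan says.** All references are to the protocol article.

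- **Question.** Secondary outcomes and questions sets a question of effect: "We will assess whether each intervention can increase the utility of the evidence retrieved". Use in care and perceived usefulness follow in the same sentence. Usefulness is to be expressed as a number needed to benefit.
- **First invitation.** The same section sends it one month after the participant's "first online exposure to one or more interventions, with one reminder after 24 hours".
- **Later invitations.** "The next invitation will be sent following the next search, but after a two-week delay".
- **End of invitations.** "This process will be repeated until one filled questionnaire for a clinical question is returned, or the trial ends".
- **Analysis.** Analysis of secondary questions states that "we will compare the distribution of answers on the IAM questionnaire", "as well as the distribution of access to the different EBM resources, using chi-squared tests". It names no other analysis of the IAM data.
- **Primary aim.** Primary outcome asks "whether each intervention increases the quantity of searches to answer questions".
- **Limitation conceded.** The Discussion allows that "these surveys may suffer from suboptimal response rates". It does not say that invitation or reply may differ between arms.

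**The concern.** A distribution of answers has respondents as its denominator. Each step into that set comes after randomisation: meeting an intervention online, searching again, and replying. Searching is also the primary outcome, and Setting and study participants names low-frequency users as the target. If an intervention works, its half may contain respondents of a different kind from those in the other half. A plain chi-squared test then mixes any change in how clinicians rate evidence with a change in who is rating it.

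This matters because the abstract names these as the secondary outcomes, and the Discussion makes a substantial effect on use and usefulness, together with sufficient utilisation, the justification for a larger multicentre trial. A difference among respondents, or its absence, could be read as a randomised result when it is not one.

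**Working it through.** **1. Figures in the document (Table 5, six baseline months).** Users with no search: 287/429 = 66.9% of postgraduates and 375/475 = 78.9% of faculty, as printed. Users with at least one search: 8 + 45 + 89 = 142 (33.1%) and 4 + 24 + 72 = 100 (21.1%). Per half of each trial that is 71 of about 214.5 postgraduates and 50 of about 237.5 faculty. If a rating needs a search, and searching stays at baseline, respondents are a minority. At an assumed 30% response they number 71 × 0.30 = 21 and 50 × 0.30 = 15 per half.

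**2. The first-invitation trigger against Table 2.** Group 8 is coded 0, 0, 0, so it has no intervention to be exposed to. For factor A the control half is Groups 5 to 8. As written, only three of these four groups can ever meet the trigger, against four of four in the other half. The same holds for B and C. Group 8 is about 429/8 = 54 postgraduates and 475/8 = 59 faculty.

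**3. What selection by searching can do.** Let a be the share of habitual searchers (0.331 or 0.211, Table 5), i the share induced to search, u the control proportion giving a favourable rating, g the true gain among habitual searchers, and v the proportion among induced searchers. With equal reply rates:

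respondent-only difference = [a(u + g) + iv]/(a + i) − u

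The values u = 0.60, i = 0.10, and all values of g and v are assumed.

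| Assumed g, v | Postgraduates | Faculty |
|---|---|---|
| g = 0, v = 0.30 | −7.0 points | −9.7 |
| g = 0, v = 0.60 | 0.0 | 0.0 |
| g = 0, v = 0.80 | +4.6 | +6.4 |
| g = +5 points, v = 0.40 | −0.8 | −3.1 |
| g = +5 points, v = 0.65 | +5.0 | +5.0 |
| g = +5 points, v = 0.80 | +8.5 | +9.8 |

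Example, postgraduates, fourth row: (0.331 × 0.65 + 0.10 × 0.40)/0.431 = 0.592, against 0.600. The bias is zero when induced searchers rate as habitual searchers in the same arm do (second and fifth rows), negative below that and positive above it.

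**4. Effect on the test.** With g = 0, v = 0.30, i = 10 to 20 points and response 50% to 100%, a two-sided 5% test (level assumed) finds the intervention worse with probability 9% to 32% in postgraduates and 11% to 39% in faculty. The nominal rate in that direction is 2.5%.

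**5. Selection by replying alone.** Suppose true proportions of 65% (intervention) and 60% (control). Satisfied users reply at 50% in both arms, dissatisfied users at 40% and 30% (all assumed). Observed: 0.65 × 0.50/(0.65 × 0.50 + 0.35 × 0.40) = 69.9%, and 0.60 × 0.50/(0.60 × 0.50 + 0.40 × 0.30) = 71.4%. No change in searching is needed.

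**6. The obvious alternative has its own bias.** Count every randomised user, with no reply taken as no event. Suppose 33% search and 50% of these benefit in both arms, and each invitation is answered independently with probability 30% (assumed). One invitation in control gives 0.33 × 0.50 × 0.30 = 5.0%. Two in the intervention arm give 0.165 × (1 − 0.70²) = 0.165 × 0.51 = 8.4%. The gap arises from invitations alone, because invitations repeat after searches.

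**The case against.** The strongest reply is that these outcomes concern evidence that was retrieved. The number needed to benefit counts patients for whom evidence was looked up, so it has no value for a clinician who retrieved none. A lower rate per respondent in a half with many new searchers would then describe that half correctly. This stands, and it limits the point to the causal reading.

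A reader might go further and infer that the planned test reverses the true direction. The documents do not support that. Take an assumed 33% searching in control with 50% reporting benefit, and 45% searching under the intervention with the added 12 points reporting 30%. Respondents show (0.33 × 0.50 + 0.12 × 0.30)/0.45 = 44.7% against 50.0%, while all randomised users show 20.1% against 16.5%. The 3.6-point gain is 0.12 × 0.30, which comes wholly from more searching, the primary outcome. No clinician's benefit per retrieval has improved. The documents give no IAM response rate, no benefit rate, and no sign that new searchers rate evidence lower.

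Nor do they say that only a user who has searched can answer. The first invitation follows exposure, and only later ones follow a search. That a search is needed is an inference from a questionnaire about retrieved evidence, and the algorithm is in Additional file 3, not shown.

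It can also be said that denominators and non-response rules belong in an analysis plan. That is fair for those details. It does not answer the mismatch between the stated question and the stated test. These are secondary outcomes in a study that likens itself to phase II, which limits the consequences but leaves the mismatch in place.

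**Conclusion.** The point holds as a limit on inference. The stated chi-squared test on returned answers does not answer the stated question of whether each intervention increases utility, use and usefulness, because entry to the analysed set depends on exposure, searching and replying after randomisation. Loss of randomised comparability follows from the invitation scheme, whatever values are assumed. The size and sign of any bias do not follow from the documents: the worked cases with i = 10 points run from −9.7 points to +6.4 points when no one's rating changes, all on assumed inputs, and the bias is zero if new searchers rate like habitual ones. The Group 8 trigger is undefined as written, subject to Additional file 3. The primary outcome is unaffected. The change is worth making because the case for a larger trial draws on these results.

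**What to change.** In Analysis of secondary questions:

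1. State that the respondent-only answer distributions and the number needed to benefit describe the evidence retrieved, and are not a randomised test of each intervention's effect.
2. Report, for A, B and C in each trial, the numbers invited, the number of invitations and the replies by arm. State how Group 8 is first invited, if Additional file 3 does not.
3. Add a supporting analysis, using the same factorial regression as the primary outcome: the proportion of all randomised users with at least one IAM-reported use of evidence, and with at least one reported or expected patient benefit.
4. State the weakness of item 3. It mixes searching, replying and benefit, and counting non-reply as no event can favour the arm that searches more. Read it beside the invitation and reply rates, for example with a sensitivity analysis limited to the first invitation, and not as the sole comparison.

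In the Discussion, the case for a larger trial should not rest on the respondent-only test alone.

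Cost: wording and a few added tables. The randomised lists, invitations and replies are handled in the automated system, so no new data collection should be needed. Trial status says that no analysis had begun when the article was submitted, so on that statement the change could still be specified in advance.

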**Table 1 Tab1:** **EBM Resources accessible through MacPLUS Federated Search (MacPLUS FS)**

	Description	Specific resources available**
**Summaries***	Summary of the body of evidence at a topic-level (not just a research question). Regularly updated (variable frequency).	DynaMed
		UpToDate
		Best Practice
	May provide actionable recommendations.	ACP PIER
**Pre-appraised research***	Continuously updated and appraised.	
Synopses of systematic	One-page description of selected reviews with commentaries from experts.	ACP Journal Club (selected via PLUS), Database of Abstracts of Reviews of Effects (DARE)
reviews		
Systematic reviews	Selected reviews rated by clinicians	McMaster PLUS (including Cochrane)
	for relevance & novelty.	
Synopses of studies	One-page description of selected	ACP Journal Club (selected via PLUS)
	studies with commentaries from experts.	
Studies	Selected studies rated by clinicians	McMaster PLUS
	for relevance & novelty.	
**Non-pre-appraised research***	Always requires independent own appraisal.	
Filtered studies	Selection of studies using empirically	Clinical Queries in PubMed
	derived methodological filters.	
Unfiltered studies	Unselected studies from large databases.	PubMed (MEDLINE)
**Alerts to new evidence updates**	Email alerts to new evidence.	McMaster PLUS
	Customized to areas of interest.	(same as BMJ EvidenceUpdates)
**Additional resources**	Available alongside the search functions.	
Single citation matcher	Helps finding specific citations.	PubMed matcher and McMasterPLUS
Clinical vital links	Prescribing information.	Compendium of Pharmaceuticals
	Patient information.	MedlinePlus
	Medical calculators and tool sets.	MedCalc3000
Other EBM links		EBM Toolbox (Oxford Centre for EBM)
	Guidance for EBM practice.	JAMAevidence (McGraw-Hill)
	Toolboxes & appraisal spreadsheets.	Centre for EBM (Univ. Health Network) Bandolier

*These layers, adapted from the 6-S pyramid of EBM resources [20],[49], are searched simultaneously in MacPLUS FS. Results are displayed on one page output in that order, *i.e*., with the most clinically useful hits at the top (see Figure 1).

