Finally, we will explore if the interventions modify the patterns of use of the different EBM resources, and in particular if they increase the accesses to higher levels of evidence, such as summaries and pre-appraised research, compared to non-pre-appraised research. Table 6 displays the baseline distribution of access across the pyramid of EBM resources among clinicians that have adopted MacPLUS FS, that is, `regular-searchers’ and `super-searchers.’ With 1,025 searches, these users have conducted about 75% of all searches in MacPLUS FS, and accessed one of its resources 1,390 times in total. All resources in the federated search were consulted: summaries were accessed 53.2% of the times, pre-appraised research in 16.1%, and non-pre-appraised research in 30.6% of the times. Postgraduates searched less summaries than faculty did (49.0% vs. 63.8%), and more non-pre-appraised resources (35.3% vs. 19.3%).

**Table 6 Tab6:** **Baseline frequency of access to EBM resources (% of all accesses), among `regular-searchers’ and `super-searchers’***

		Postgraduates	Faculty	Total
		(n = 53)	(n = 28)	(n = 81)
		739 searches	286 searches	1,025 searches
**Summaries**		**485 (49.0%)**	**255 (63.8%)**	**740 (53.2%)**
	DynaMed	174 (17.6%)	39 (9.8%)	213 (15.3%)
	UpToDate	120 (12.1%)	128 (32.0%)	248 (17.8%)
	Best Practice	147 (14.8%)	71 (17.8%)	218 (15.7%)
	ACP PIER	44 (4.4%)	17 (4.3%)	61 (4.4%)
**Pre-appraised research**		**156 (15.8%)**	**68 (17.0%)**	**224 (16.1%)**
	Synopses of systematic reviews	23 (2.3%)	17 (4.3%)	40 (2.9%)
	Systematic reviews	66 (6.7%)	21 (5.3%)	87 (6.3%)
	Synopses of studies	10 (1.0%)	4 (1.0%)	14 (1.0%)
	Studies	57 (5.8%)	26 (6.5%)	83 (6.0%)
**Non-pre-appraised research**		**349 (35.3%)**	**77 (19.3%)**	**426 (30.6%)**
	Filtered studies	257 (26.0%)	60 (15.0%)	317 (22.8%)
	Unfiltered studies	92 (9.3%)	17 (4.3%)	109 (7.8%)
**Total number of accesses**		**990 (100%)**	**400 (100%)**	**1,390 (100%)**

**i.e*., clinicians who conducted more than one search per month on average.

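### The secondary questions ask about an increase in higher-level evidence and extent of use, but the only named test is a chi-squared comparison of distributions, which ignores direction

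*Protocol article*

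**What the plan says.** Protocol article, Secondary outcomes and questions, sets two kinds of access question. The first has no direction: "we will explore if the interventions modify the patterns of use of the different EBM resources". The second does: "in particular if they increase the accesses to higher levels of evidence", and it names its contrast, "such as summaries and pre-appraised research, compared to non-pre-appraised research". The layers are ordered by the article itself; the footnote to Table 1 says that results are displayed "with the most clinically useful hits at the top".

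The questionnaire aims are also worded as increases: "We will assess whether each intervention can increase the utility of the evidence retrieved". They include "the use of the evidence (the extent of use when caring for a specific patient". Perceived usefulness has its own summary, the number needed to benefit.

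Under Analysis of secondary questions, one method covers both sets: "we will compare the distribution of answers on the IAM questionnaire", "as well as the distribution of access to the different EBM resources, using chi-squared tests". The article does not say how many categories enter the access test, names no directional contrast, and gives no alpha or power for these tests.

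**The concern.** A Pearson chi-squared test on more than two categories treats them as unordered labels. A small p-value says that two distributions differ somewhere. It does not say that a larger share of accesses went to higher-level evidence, which is the question asked in particular. Two things follow.

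- **Interpretation.** The test can be significant with no movement between layers, or with movement downwards.
- **Power.** If the true effect is a steady upward shift, the signal is spread over several degrees of freedom and power falls.

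Quality of searching is one half of the stated study aim (Study aims), and this is the only test named for the evidence-level question. The choice of test therefore bears on what the trial can say about that half.

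**Working it through.** The article gives no figure for these tests, so there is nothing of its own to reproduce beyond Table 6. Its layer shares follow from its counts: postgraduates 485/156/349 of 990 = 49.0/15.8/35.3%; faculty 255/68/77 of 400 = 63.8/17.0/19.3%.

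**Assumptions throughout:** two-sided alpha 0.05 (not stated in the article), equal arms, independent accesses. The last does not hold in practice: Table 6 has 1,390 accesses from 81 users, or 1,390/81 = about 17 each. The sample sizes below are therefore effective sizes.

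**1. Rejection with layer shares unchanged.** One arm has the postgraduate distribution over the ten resources. The other keeps the postgraduate layer totals but splits summaries as faculty do (39/128/71/17 of 255).

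| Summary | Arm 1 | Arm 2 |
|---|---|---|
| DynaMed | 17.6% | 7.5% |
| UpToDate | 12.1% | 24.6% |
| Best Practice | 14.8% | 13.6% |
| ACP PIER | 4.4% | 3.3% |

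The other six rows are identical. In 20,000 simulated trials the ten-row chi-squared (df 9) rejects in 85% at 200 accesses per arm and 93% at 250. The three-layer test rejects in 5%, as it should.

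**2. Significance for a downward shift.** Three layers (summaries, pre-appraised, non-pre-appraised), illustrative counts 242/78/175 against 205/78/212, 495 per arm. Expected counts are 223.5/78/193.5, so

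chi-squared = 2 × 18.5²/223.5 + 0 + 2 × 18.5²/193.5 = 3.06 + 3.54 = 6.60, df 2, p = 0.037.

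Summaries fell from 48.9% to 41.4%.

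**3. Power for a steady upward shift.** A 1-df test has 80% power at noncentrality 7.849. If the whole effect lies along the order, the omnibus test has about the same noncentrality with more degrees of freedom:

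| df | 5% critical value | Power |
|---|---|---|
| 1 | 3.84 | 80.0% |
| 2 (three layers) | 5.99 | 70.9% |
| 9 (ten resources) | 16.92 | 44.6% |

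The losses are 9.1 and 35.4 points.

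**4. How far the loss depends on the shape of the effect.** All at 250 accesses per arm.

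| Effect | Ranked three-layer mean score | Three-layer chi-squared | 2x2: higher-level v. non-pre-appraised |
|---|---|---|---|
| Postgraduate split, common odds ratio 1.5 upwards | 65% | 55% | 55% |
| Faculty split, common odds ratio 1.5 upwards | 56% | 47% | 39% |
| 10 points from non-pre-appraised to pre-appraised (49/15.7/35.3 to 49/25.7/25.3) | 25% | 82% | 68% |

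For the last row the noncentralities are 1.65 (df 1), 10.16 (df 2) and 5.92 (df 1). No test is best in every row. The ranked score does badly when users move into the middle layer. The 2x2 has no degrees-of-freedom penalty, but it uses only one cut, so it gives up power when the effect also lies at the other.

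**The case against.** The strongest reply has four parts.

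**The contrast is already worded.** Summaries and pre-appraised research are set together against non-pre-appraised research. Run as a 2x2 chi-squared, that has 1 df and no penalty. This stands against any fixed power loss. A reader might infer that the plan loses 9 to 35 points, but the article does not fix the number of categories, and the figure needs a steady shift, an 80% reference and 3 to 10 categories. It does not remove the point, because the analysis section never assigns a test to that contrast.

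**A ranked score is no better.** A reader might conclude that chi-squared should give way to a score placing summaries above pre-appraised research. The documents do not support this: the directional question groups the two, and the videos and badges (Table 4; Intervention C) also promote the middle layer. Under the move in the last row of step 4, the ranked score has 25% power against 82% for chi-squared. This stands.

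**A change within summaries is a real finding.** The article also asks about any change in pattern, and for that question rejecting in step 1 is correct. This stands: the 85% is not a false-positive rate of the plan. It becomes an error only if the result is read as an answer to the evidence-level question.

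**Direction can be read from a table, and the analysis is exploratory.** For three percentages this is largely fair. For ten resources, a significant omnibus p-value beside a small difference in layer shares gives no test of that difference. The exploratory status limits the consequence.

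For the questionnaire, the response options are in an additional file not shown. That extent of use is graded is inferred from its wording, so only a conditional recommendation can be made.

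**Conclusion.** The mismatch is real but modest. The article asks directional questions about evidence level, utility and extent of use, and names only a test that ignores direction. A significant ten-resource result may reflect no change in layer shares (about 85% rejection at 200 independent accesses per arm in the scenario shown), and a significant three-layer result may reflect a downward shift.

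The power loss is conditional: 80% becomes 71% at df 2 and 45% at df 9 for a steady upward shift, with two-sided alpha 0.05 and independent observations. It is nil in degrees-of-freedom terms for the 2x2 contrast, and chi-squared outperforms a ranked score when users move into the middle layer. Chi-squared remains right for the question about any change in pattern. The consequence is confined to secondary and exploratory conclusions on the quality of searching; the primary outcome is untouched.

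**What to change.** In Analysis of secondary questions:

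1. Keep the chi-squared comparison of access for any change in the pattern of use, with a correction for repeated accesses within users.
2. Name, as the test of the evidence-level question, a 1-df regression of access type (summaries or pre-appraised, against non-pre-appraised) on the three intervention dummies, with standard errors clustered on user. The sign of each coefficient then gives the direction.
3. For questionnaire items with graded responses, use proportional-odds regression or a mean-score test. Keep chi-squared for nominal items, and the number needed to benefit for perceived usefulness.

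The cost is a few sentences and one additional secondary test, with no new data. Trial status says that no analysis has begun, so the change can be made before results are known. The 1-df contrast gives up some power if the effect lies mainly between summaries and pre-appraised research; the retained omnibus comparison and a Table 6 layout would still show that.
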